# Bump2Baby and Me: protocol for a randomised trial of mHealth coaching for healthy gestational weight gain and improved postnatal outcomes in high-risk women and their children

**DOI:** 10.1186/s13063-021-05892-4

**Published:** 2021-12-28

**Keywords:** Pregnancy, Gestational diabetes, Obesity, mHealth, Implementation, Postpartum, Health coaching, Maternal health, Weight management, Foetal programming

## Abstract

**Background:**

Gestational diabetes (GDM) impacts 8–18% of pregnancies and greatly increases both maternal and child risk of developing non-communicable diseases such as type 2 diabetes and obesity. Whilst lifestyle interventions in pregnancy and postpartum reduce this risk, a research translation gap remains around delivering implementable interventions with adequate population penetration and participation. Impact Diabetes Bump2Baby is an implementation project of an evidence-based system of care for the prevention of overweight and obesity. Bump2Baby and Me is the multicentre randomised controlled trial investigating the effectiveness of a mHealth coaching programme in pregnancy and postpartum for women at high risk of developing GDM.

**Methods:**

Eight hundred women will be recruited in early pregnancy from 4 clinical sites within Ireland, the UK, Spain, and Australia. Women will be screened for eligibility using the validated Monash GDM screening tool. Participants will be enrolled from 12 to 24 weeks’ gestation and randomised on a 1:1 basis into the intervention or control arm. Alongside usual care, the intervention involves mHealth coaching via a smartphone application, which uses a combination of synchronous and asynchronous video and text messaging, and allows for personalised support and goal setting with a trained health coach. The control arm receives usual care. All women and their children will be followed from early pregnancy until 12 months postpartum. The primary outcome will be a difference in maternal body mass index (BMI) of 0.8 kg/m^2^ at 12 months postpartum. Secondary maternal and infant outcomes include the development of GDM, gestational weight gain, pregnancy outcomes, improvements in diet, physical activity, sleep, and neonatal weight and infant growth patterns. The 5-year project is funded by the EU Commission Horizon 2020 and the Australian National Health and Medical Research Council. Ethical approval has been received.

**Discussion:**

Previous interventions have not moved beyond tightly controlled efficacy trials into routine service delivery. This project aims to provide evidence-based, sustainable support that could be incorporated into usual care for women during pregnancy and postpartum. This study will contribute evidence to inform the early prevention of non-communicable diseases like obesity and diabetes in mothers and the next generation.

**Trial registration:**

Australian New Zealand Clinical Trials Registry ACTRN12620001240932. Registered on 19 November 2020

**Supplementary Information:**

The online version contains supplementary material available at 10.1186/s13063-021-05892-4.

## Background

Gestational diabetes (GDM), defined as high blood glucose levels during pregnancy, is an increasing health problem affecting up to 13% of pregnancies worldwide and approximately 17 million births annually [1]. Women with a prior history of GDM are almost 10 times more likely to develop type 2 diabetes (T2DM) over the next 10 years [2]. Excess weight is a known risk factor for T2DM; however, excess gestational weight gained during pregnancy is frequently not lost postpartum due to the many demands on a new mother. This leads to an increased risk of overweight and obesity, GDM in future pregnancies, and T2DM later in adult life [3]. This risk is not confined to just the mother. Early foetal programming means that children born to women with obesity during pregnancy also have higher risks of developing childhood overweight and obesity [4–6]. A multicomponent, life course approach with a focus on prevention and early detection is required to break this cycle and reduce the population burden of diabetes [7].

Strong evidence shows that lifestyle change, with improvements in diet and physical activity level, can reduce the development of T2DM in people at risk [8, 9]. Lifestyle interventions during pregnancy demonstrate optimised gestational weight gain (GWG) with an associated reduction in the risk of GDM [10, 11]. Furthermore, a meta-analysis and behaviour change taxonomy analysis showed the value of interventions with components that target diet, physical activity, and behaviour [12–14]. Pregnancy is a key time to initiate engagement as women are involved with health services and trusted health care professionals during this period. However, it has been well documented that during the postpartum period, women experience a lack of professional support and continuity of care [15]. This can result in significant challenges in terms of engaging women in lifestyle interventions, particularly without prior engagement in pregnancy. As such, the perinatal period represents an important opportunity for developing lifestyle changes during pregnancy and ensuring these are maintained after birth. Whilst lifestyle modifications have proven effective [16–18], there remains a large research translation gap around achieving implementable interventions with adequate population penetration and participation. Effective preventative interventions to date have not moved beyond the research phase to consider implementation into routine service delivery, and novel strategies are required [19, 20].

Smartphones have high-level penetration across socioeconomic groups and provide a convenient and accessible method through which to engage and motivate women to improve lifestyle behaviours. Almost 90% of people in the UK and Spain own a smartphone with similarly high penetrations reported for other EU countries and Australia [21]. In addition, mothers aged 18–49 years spend an estimated 21 h per week on their smartphones [22]. Apps and mHealth can provide ‘around the clock’ information, as well as tailored support at low cost [23]. Recent evaluations of mHealth apps available in pregnancy revealed a large number but few were high quality. They typically used a very small range of behaviour change techniques, and the evidence-based nutrition and physical activity information provided was equally limited [24, 25]. Women with low socioeconomic status commonly use apps during pregnancy but not postpartum because of the lack of quality apps [26]. This highlights the opportunity for intervention delivery through a high-quality, evidence-based app to provide maternal support during pregnancy and postpartum. This mode of delivery could facilitate an affordable intervention with reach and scale to overcome penetration and participation challenges as well as enable tailored support to be delivered on a large scale.

The Bump2Baby and Me study is a multicentre randomised controlled trial (RCT) that aims to investigate the implementation and effectiveness of an mHealth-supported behavioural change coaching programme for women who are at high risk of developing GDM. This RCT is central to an international project designed to demonstrate the real-world implementation of an evidence-based, effective system of care for the prevention of diabetes, overweight, and obesity when delivered across antenatal settings (Impact Diabetes Bump2Baby). The Bump2Baby and Me RCT integrates best practice evidence from previous RCTs that successfully reduced excess weight gain to inform personalised health coaching which is delivered via a smartphone application [16, 17, 27]. This RCT proposes to bridge the health service gap from pregnancy to postpartum using a low-resource, precision medicine, evidence-based intervention. This study aims to evaluate the implementation and effectiveness of the mHealth coaching programme to improve appropriate maternal weight management during pregnancy and postpartum and impact on the growth of the baby, which will contribute to early prevention of maternal and child diabetes, overweight, obesity, and other non-communicable diseases.

## Methods

### Study design and setting

Bump2Baby and Me is a multicentre single-blind randomised controlled trial involving 800 pregnant women to investigate an mHealth coaching programme for those who are at high risk of developing GDM. This study involves five hospital sites across four countries: National Maternity Hospital in Dublin, Ireland; Clinical University Hospital San Cecilio and Mother-Infant University Hospital in Granada, Spain; Southmead North Bristol NHS Trust in Bristol, England; and Monash Medical Centre in Melbourne, Australia. Ethical approval has been granted for all study sites. This RCT was registered prospectively on the Australian New Zealand Clinical Trials Registry, trial registration number ACTRN12620001240932, on 19 November 2020. The study flow design is described in Fig. 1.

**Fig. 1 Fig1:**
[figure not shown]
Flow chart with an overview of the time points and data collected in the Bump2Baby and Me study

This protocol is reported in accordance with the Standard Protocol Items: Recommended items to address in a clinical trial protocol and related documents (SPIRIT) guidelines. The SPIRIT checklist is available in Additional file 1, and the timeline figure is detailed in Fig. 2.

**Fig. 2 Fig2:**
[figure not shown]
Standard Protocol Items: Recommendations for Interventional Trials (SPIRIT) timeline providing information about participant enrolment, intervention, and outcomes evaluated during the trial according to SPIRIT recommendations

### Population

Pregnant women aged 18 and older attending maternity services within any of the hospital sites will be screened for their risk of developing GDM using the validated Monash GDM Screening Tool [28] upon referral to the hospital by the research staff. Individuals scoring at risk (3 or higher) will be further assessed as to whether they meet the additional study criteria.

The following are the inclusion criteria:
Women attending one of the five participating maternity hospitals for their maternity careWomen identified at high risk of developing GDM: defined by the Monash GDM Screening Tool score of 3 or higher [28]Women less than 24 weeks’ gestationWomen owning a smartphone capable of hosting the intervention appWomen not currently participating in any other lifestyle-related clinical trial

The following are the exclusion criteria:
Established diabetes (T1DM or T2DM), previously knownCurrent multiple pregnancy (e.g. twin, triplets)Cancer (not in remission)Severe mental illness in the last 3 monthsSubstance abuse (illicit drugs) in the last 3 monthsMyocardial infarction in the last 3 monthsInability to verbally communicate in English for the Irish, English, and Australian sites and inability to verbally communicate in Spanish for the Spanish site

If a woman is deemed eligible for study inclusion by the research team, they will receive a preliminary participant information sheet about the study and have the opportunity to discuss with a member of the research team before providing written informed consent and enrolling in the study. As the trial and intervention are embedded in usual antenatal care, some site-specific adaptations were made which are highlighted in the figure and methods where relevant.

### Randomisation procedure

Participants will be randomised to the intervention or control group at enrolment to the study in advance of their first antenatal visit. The randomisation will be generated centrally by the trial biostatistician using a computer-generated random sequence on a 1:1 basis using block randomisation of 200 participants for each site. Allocation will be recorded in sequentially numbered and sealed, opaque envelopes, distributed to study sites. For each participant, the researcher at each site will select and open the next sequential envelope, with an independent witness and co-sign the envelope. As the Melbourne site delivers their first antenatal appointment online, the randomisation sequence will be embedded into the study management database and each participant will be assigned sequentially as they are registered to the study. The envelopes for this site will be retained as a randomisation quality check. At the first study visit, participants will receive an arm-specific information sheet and have further opportunities to ask any questions. Informed written consent to participate will then be secured. Throughout the study, individual participants will only be provided with the information relevant to their arm of the study and will not be made overtly aware of their allocation to control or intervention groups. Study clinicians who are providing services to the participants and researchers carrying out data collection will not be informed by the research team as to their allocation to control or intervention groups.

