### Baseline assessments

Participants will attend the first study visit after recruitment in line with routine antenatal care. A researcher will facilitate participants in the intervention group with onboarding, including downloading the mHealth coaching app, account creation, and scheduling the initial coaching session. For participants in the control group, the research clinician will provide the women with a written leaflet with details of the approved website and show the woman how to access the health information on the Bump2Baby website. Demographic characteristics will be collected via questionnaire and will include maternal age, ethnicity, gravidity, parity, relationship status, educational attainment, employment status (of the participant and relevant partner), housing status, childcare responsibilities, and prior medical history.

Anthropometric measurements of maternal height (cm) and weight (kg) will be extracted from medical records, and all participants will also be provided with a set of digital scales (Smart Body Fat Scale, RENPHO©) for the duration of the study. Participants will be provided with a manual on how to use the scales appropriately and will be asked to weigh themselves approximately once a week. The scales will connect via Bluetooth, with an app on the participant’s phone, which facilitates automatic recording of this data when the individual is connected to a wireless network. Body mass index (BMI, kg/m^2^) will be calculated from these measurements. Blood pressure will also be measured using a calibrated blood pressure monitor at the baseline visit.

Participants will be asked to complete the online questionnaires, detailed in Table 1, within 1 week of the baseline visit before the first health coaching session for the intervention group.

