### Statistical analyses

The intervention arm will be tested against usual care. Intention-to-treat (ITT) and a per-protocol set (PPS) analysis will be planned for both primary and secondary outcomes. Full analysis set is defined according to the ITT principle and will consist of all randomised subjects analysed according to the study arm to which they were assigned at randomisation, except for subjects who were randomised to the study in error and were subsequently excluded, e.g. twin pregnancies. The per-protocol set (PPS) will consist of all patients in the full analysis set without a major protocol deviation. Major protocol deviations include, but are not limited to, the following:
The subject was assigned to the intervention arm but did not reach minimum exposure. The minimal exposure requirement is that participants received the first onboarding session with the health coach.The subject did not have a post-baseline assessment.An eligibility criterion that was deemed to have been met at the time of randomisation was later found not to have been met.

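### The protocol gives two incompatible orders for written consent and allocation; under the randomisation section's order, refusals, and with them the analysed population, can depend on arm, as can self-reported baselines

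*Protocol article*

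**What the plan says.** Two sections of the protocol article describe consent.

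- **Population.** An eligible woman receives a preliminary information sheet and will "have the opportunity to discuss with a member of the research team before providing written informed consent and enrolling in the study". Written consent comes before, or at, enrolment.
- **Randomisation procedure.** "Participants will be randomised to the intervention or control group at enrolment to the study in advance of their first antenatal visit". Then: "At the first study visit, participants will receive an arm-specific information sheet and have further opportunities to ask any questions". Then: "Informed written consent to participate will then be secured". Written consent comes after allocation and after arm-specific information.

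Three other sections matter.

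- **Baseline assessments.** "Participants will attend the first study visit after recruitment in line with routine antenatal care". At that visit intervention women download the app, open an account and book their first coaching session. The online questionnaires are due "within 1 week of the baseline visit before the first health coaching session for the intervention group". Height and weight are taken from medical records.
- **Statistical analyses.** The full analysis set "will consist of all randomised subjects analysed according to the study arm to which they were assigned at randomisation". The only exception is women randomised in error, with twin pregnancy as the example.
- **Discussion.** Recruitment is remote at every site except Granada, and the first study visit is held within the routine antenatal visit. This fits the order in the randomisation section.

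**The concern.** Randomisation makes the arms comparable at the moment of allocation. If women decide whether to take part after that moment, knowing what they have been offered, the women who remain may differ between arms before follow-up starts. An intention-to-treat analysis guards against this only if everyone allocated stays in the analysis. A woman who has not consented cannot supply follow-up data, and multiple imputation has little to work with if her baseline data may not be used either.

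The questionnaires raise a second, smaller issue. Diet, physical activity, mood, sleep and health literacy are self-reported. An intervention woman who already has the app and a coaching appointment may answer differently from one given a leaflet and a website address. The analysis section plans comparisons of baseline with 12 months within a repeated-measures model, so a baseline that depends on arm would enter any change-from-baseline estimate.

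**Working it through.** **Order of steps**

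| Step | Population section | Randomisation and Baseline sections |
|---|---|---|
| 1 | Preliminary sheet and discussion | Enrolment and allocation |
| 2 | Written consent | First visit: arm-specific sheet |
| 3 | Enrolment | Written consent |
| 4 | – | App set-up and coaching booking (intervention), or leaflet and website (control), at the same visit |
| 5 | – | Questionnaires within 1 week of the visit |

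The columns disagree on whether written consent precedes allocation. They do not disagree on the sheet or the questionnaires. On the natural reading both follow allocation, whichever consent order applies.

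**Analysis set.** A woman who declines at step 3 was randomised and was not randomised in error, so the definition keeps her. If she also gave written consent beforehand, as the Population section implies, her data may be usable. If not, no stated rule covers her.

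**Size of a refusal bias.** The plan gives no refusal rate and no BMI for women who refuse, so there is no figure of its own to reproduce. The Sample size section supplies SD 2 kg/m², a target difference of 0.8 kg/m², 400 per arm and 70% retention. Hence 400 × 0.70 = 280 analysed per arm.

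Let r be the proportion refusing in an arm and D the BMI gap between refusers and consenters, taken as equal in both arms. The consenters' mean departs from the mean of all women allocated to that arm by r × D, so:

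bias = (difference in r between arms) × D

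The following are assumptions: a difference in r of 5 to 10%, and D of 1 to 3 kg/m² (0.5 to 1.5 of the protocol's SD).

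- 0.05 × 1 = 0.05 kg/m²; 0.05 / 0.8 = 6% of the target
- 0.10 × 1 = 0.10 kg/m²; 12.5% of the target
- 0.10 × 2 = 0.20 kg/m²; 25% of the target
- 0.10 × 3 = 0.30 kg/m²; 37.5% of the target

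**Effect on the test.** SE = 2 × √(2/280) = 0.169. With no true effect, the two-sided rejection rate at a shift b is Φ(−1.96 + b/SE) + Φ(−1.96 − b/SE).

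| Shift b (kg/m²) | b/SE | Type I error |
|---|---|---|
| 0.05 | 0.30 | 6.0% |
| 0.10 | 0.59 | 9.1% |
| 0.20 | 1.18 | 22% |
| 0.30 | 1.77 | 43% |

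**Power is not the issue.** Refusal of 10% in one arm and 20% in the other leaves 400 × 0.9 × 0.7 = 252 and 400 × 0.8 × 0.7 = 224 analysed. Power for 0.8 at SD 2 is still about 99%.

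**The case against.** The best defence is that the two sections describe a two-stage consent: a first written consent on the preliminary sheet, then a confirmatory one after allocation. Women unwilling to join would mostly leave before the envelope is opened. The flow chart and timeline figures, which might settle the order and show site adaptations, are not visible in the text at hand. This is a fair reading. A reader might infer from the randomisation section alone that the all-randomised set cannot be formed. The documents do not support that: it would take at least one refusal after allocation with no earlier consent covering her data. The conflict still stands, because the text does not say that there are two consents or what the first one covers.

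Arm-specific sheets also serve masking. Women receive only their own arm's information and are not openly told which arm they are in. A control woman who does not know what she is missing has less reason to refuse. That weakens the mechanism without removing it: intervention women may still decline because of burden, and the content of the preliminary sheet is unknown.

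A reader might also infer that the primary outcome's baseline is contaminated. It is not, to any extent the text shows. Baseline height and weight come from records, the primary outcome is BMI at 12 months, and site is the only covariate expected. The questionnaires precede the first coaching session, and Table 1 marks 12 months as the time point of interest for maternal measures collected repeatedly. The baseline issue is therefore modest and confined to secondary outcomes.

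Finally, the 22% error rate is tempting as a headline. The arithmetic is right, but the 0.2 shift needs, for example, 10% differential refusal and a gap of a full SD. At a 1 kg/m² gap the rate is about 6 to 9%.

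**Conclusion.** The protocol contradicts itself on whether written consent precedes allocation, and the section that governs randomisation has the order that lets refusal depend on arm. The full analysis set names no treatment for a woman who declines after allocation. These points rest on the text alone.

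The size of any bias cannot be known from the documents. Under the assumptions shown it is 0.05 to 0.30 kg/m² in 12-month BMI; with no differential refusal, or no gap between refusers and consenters, it is zero. A larger sample would not reduce it. For questionnaire outcomes, self-reported baselines can be influenced by arm on the natural reading of either consent order, but no amount can be given.

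**What to change.** **Women not yet randomised.** Reconcile the Population and Randomisation sections to one order:

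1. Preliminary sheet and discussion.
2. Written consent to randomisation and data use on that sheet.
3. Online baseline questionnaires.
4. Opening of the envelope, or release of the database allocation in Melbourne.
5. Arm-specific sheet and onboarding.

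Giving the arm-specific sheet last keeps the masking aim. The steps all exist already, and the questionnaires are already online.

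**Women already randomised.**

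- State which consent order each site used.
- Count refusals after allocation as randomised, and report them by arm in the participant flow.
- Say how the full analysis set treats them.
- Add a bounding sensitivity analysis for 12-month BMI, using only data whose use is permitted.
- Base questionnaire comparisons on the 12-month values, not on change from a baseline collected after allocation.

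**Cost.** Re-ordering means a short delay before allocation and an ethics amendment at the sites; the preliminary sheet may need more text to support consent to randomisation. Its reach is limited: recruitment began on 9 February 2021 and was due to end by February 2022, and the article appeared on 28 December 2021. Reporting refusals by arm costs almost nothing and remains useful whatever the recruitment status.
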